### Interim analyses

8.2

It is not expected that data will be analyzed for all participants until the end of the study.

### Methods for additional analyses (e.g. subgroup analyses)

8.3

N/a

### Methods in analysis to handle protocol non-adherence and any statistical methods to handle missing data

8.4

Missing data and any data collected that is not in compliance with the protocol will be removed from the data analysis.

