##### Withdrawal or dropout criteria

4.1.1.3

- Participants with incomplete or false information.

- Participants with adverse events.

- Participants who are not suitable for continuing treatment due to other systemic diseases for various reasons.

- Participants who voluntarily proposed to withdraw from the study.

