#### Criteria for discontinuing or modifying allocated interventions

4.2.3

For patients with PSD who received the aromatherapy inhalation intervention, if a serious adverse reaction (e.g., an allergic reaction) occurs during the treatment, the research team will immediately stop the treatment for that participant and carry out the necessary medical interventions. At the same time, if the participant voluntarily requests to stop the treatment, we will record his/her request and respect his/her decision. Participants’ depressive symptoms will be regularly assessed in the study and adjustments to the treatment regimen will be considered if significant improvement or worsening is observed. All these adjustments will be made under the guidance of the research ethics committee to ensure that the safety and rights of the participants are protected.

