#### Primary outcome measures

4.3.1

1. Recruitment rates: Recruitment rates will be calculated as the proportion of successfully recruited eligible participants within the specified period, documented weekly, and reported as a percentage of the total planned recruitment. A recruitment rate of at least 70% will be considered acceptable.

2. Intervention adherence: Intervention adherence will measure the proportion of participants who complete the intervention as planned. This will be tracked using participant logs that record the completion of each aromatherapy session, CBT session, and conventional treatment session. Adherence to each component will be reported weekly. An adherence rate of at least 80% will be considered acceptable. Additionally, feasibility outcomes will include the proportion of participants who complete all assessments as scheduled, assessing the practicality of integrating aromatherapy with existing treatments.

3. Assessment completion: Assessment completion will assess the proportion of participants who complete all scheduled assessments and follow-ups. This will be calculated and reported at the end of the intervention. A completion rate of at least 85% will be considered acceptable.

5. Safety Assessment: Safety will be evaluated through subjective and objective measures. Participants will report any discomfort or adverse reactions, and vital signs (heart rate, respiratory rate, blood pressure) will be monitored before and after each session. An adverse event log will document all incidents and management actions. Adverse reactions will be categorized as mild, moderate, or severe.

- Moderate: Noticeable symptoms that may interfere with daily activities but are not life-threatening, requiring medical intervention or short-term observation.

- Severe: Symptoms significantly impacting daily life, potentially life-threatening, requiring intensive medical intervention such as hospitalization or emergency medication.

An acceptable safety threshold is set at no more than 10% of participants experiencing moderate to severe adverse reactions.

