#### Primary outcome analysis: feasibility metrics

8.1.1

Recruitment, adherence, and completion rates will be the focus, analyzed descriptively to provide insights into the practical implementation and scalability of the intervention. Each metric will be reported as a percentage:

- Recruitment rate: Proportion of eligible participants who were successfully recruited.

- Intervention adherence: Proportion of participants who adhered to the intervention throughout the study.

- Assessment completion: Proportion of participants who completed all assessments and follow-ups.

- Safety assessment: Safety will be evaluated through subjective and objective measures, including monitoring vital signs and documenting adverse reactions.

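### Section 8.4 deletes missing and non-compliant data with no outcome exempted, which contradicts the primary adherence and completion definitions and leaves only a complier, complete-case basis for the clinical comparisons

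*Protocol article*

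**What the plan says.** The whole rule on missing data and non-adherence in the protocol article is one sentence in section 8.4: "Missing data and any data collected that is not in compliance with the protocol will be removed from the data analysis". It makes no exception for the feasibility outcomes. It names no all-randomised set and no sensitivity analysis.

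Section 4.3.1 defines the primary outcomes. For adherence: "Intervention adherence will measure the proportion of participants who complete the intervention as planned", tracked by session logs, and "An adherence rate of at least 80% will be considered acceptable". For completion: "Assessment completion will assess the proportion of participants who complete all scheduled assessments and follow-ups", and "A completion rate of at least 85% will be considered acceptable". Section 8.1.1 repeats completion as "Proportion of participants who completed all assessments and follow-ups". Section 4.5 says these criteria help to judge whether a full-scale trial is feasible, alongside a 70% recruitment criterion. Section 4.3.1 adds a safety threshold: at most 10% of participants with moderate to severe reactions.

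For the clinical scales, section 8.1.2 plans descriptive summaries at each time point and also a non-inferiority comparison of aromatherapy with CBT. Section 4.1.1.3 lists adverse events and voluntary withdrawal among the reasons for withdrawal or dropout.

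**The concern.** An adherence rate has to count the people who did not adhere, and a completion rate has to count the people with missing assessments. Section 8.4 tells the analyst to remove the data that identify both. Followed to the letter for these outcomes, it removes the failures from the denominator as well as from the numerator, and two of the pre-set criteria become automatic passes.

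For the clinical scales and the comparison with CBT, the rule defines the analysed group by what happened after randomisation. Comparability of the arms then no longer rests on randomisation alone. Because no other analysis set is named, a reader of the results could not see how much the deletion mattered.

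**Working it through.** **1. The plan's own figure.** Section 4.5 takes about 30 per group and adds 10% for dropout: 30 × 1.10 = 33, and 3 × 33 = 99. This reproduces. Dividing instead gives 30/0.9 = 33.3, which is consistent with a figure the plan calls approximate. Nothing below depends on the difference.

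**2. The feasibility rates under the two readings.** Let *a* be the number of successes among *n* randomised. The definitions in 4.3.1 and 8.1.1 give *a/n*. Literal deletion of the failures under 8.4 gives *a/a* = 100%, whatever *a* is. The counts below are illustrative, with *n* = 33 from section 4.5.

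| Outcome | All randomised | Criterion | After deletion |
|---|---|---|---|
| Adherence, 24 adherent | 24/33 = 72.7% | 80%, missed | 24/24 = 100% |
| Adherence, 26 adherent | 26/33 = 78.8% | 80%, missed | 26/26 = 100% |
| Completion, 28 complete | 28/33 = 84.8% | 85%, missed | 28/28 = 100% |

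A partial reading, in which only non-adherers are removed, can also move completion across its criterion. Assume 80% adhere, and that completion is 95% in adherers and 40% in non-adherers. Completion in everyone is 0.80 × 0.95 + 0.20 × 0.40 = 0.84, which misses 85%. In adherers alone it is 0.95, which passes.

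**3. How many remain for the clinical summaries.** Suppose adherence and completion sit exactly at their criteria and 8.4 removes both kinds of failure.
- Independent failures: 33 × 0.80 × 0.85 = 22.4 per arm, or 99 × 0.80 × 0.85 = 67.3 in total.
- Failures that never overlap: 33 × (0.80 + 0.85 − 1) = 21.5 per arm, or 64.4 in total.
- Failures that overlap fully: 33 × 0.80 = 26.4 per arm, or 79.2 in total.

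Section 4.5 intended about 30 per arm after dropout.

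**4. What deletion does to a clinical mean.** Let *f* be the fraction deleted in an arm and *g* the mean improvement in retained minus deleted participants. The mean over everyone is (retained mean) − *f* × *g*, so deletion shifts the arm mean by *f* × *g*. The shift in a contrast between arms is *f*₁*g*₁ − *f*₂*g*₂, or (*f*₁ − *f*₂) × *g* if the gap is the same in both. The documents give neither *f* by arm nor *g*, so the PHQ-9 values below are assumptions.

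| Deleted, arm 1 vs arm 2 | Gap *g* (points) | Shift in contrast |
|---|---|---|
| 20% vs 20% | 3 | 0 |
| 20% vs 10% | 3 | 0.10 × 3 = 0.30 |
| 20% vs 5% | 3 | 0.15 × 3 = 0.45 |
| 30% vs 10% | 3 | 0.20 × 3 = 0.60 |
| 20% vs 5% | 5 | 0.15 × 5 = 0.75 |
| any | 0 | 0 |

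A negative gap, where those who improve are the ones who stop, reverses the sign.

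**The case against.** The strongest reply is that 8.4 removes data, not people. The specific definitions in 4.3.1 and 8.1.1 speak of proportions of participants, and every session is logged. A missed session in a log is an observed non-adherence, not a missing value. A sensible analyst would keep everyone in the denominator. This stands as far as it goes: 100% is what 8.4 produces if it is applied to these metrics, not what must happen. It does not remove the contradiction, because the document does not say that the specific definition prevails, and the heading of 8.4 names non-adherence directly.

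Several stronger readings are tempting but not supported:

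- **That the 80% and 85% criteria alone decide on the full trial.** Section 4.5 says the criteria help to determine feasibility. Recruitment and safety also have thresholds, and those do not become automatic passes by the same arithmetic.
- **That section 4.2.3 makes deletion depend on outcome.** It says that "adjustments to the treatment regimen will be considered if significant improvement or worsening is observed". An adjustment that the protocol allows is not non-compliance with it, so 8.4 does not delete those data on its terms.
- **That the withdrawal criterion "Participants with incomplete or false information" covers missed assessments.** It may concern the information that participants supply; the text does not equate the two.
- **That every efficacy summary is biased, in favour of aromatherapy.** Section 4 of the working shows that bias needs a link between removal and outcome, and for a contrast also a difference between arms. Daily sessions are a heavier schedule than two a week. But all patients are inpatients, physicians accompany the aromatherapy sessions, the discussion expects the familiar plant powders to help compliance, and the introduction describes CBT as demanding for patients. The only dropout figure, 10%, is the same for all arms.

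A per-protocol set is also a usual companion in a non-inferiority comparison. The fault is that it is the only set stated.

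**Conclusion.** The rule is wrong as written. It contradicts the definitions of two primary outcomes, and if it is applied to them it turns any true rate into 100%, so that neither criterion could fail. That result is pure arithmetic and rests on one condition only: that 8.4 is taken to override 4.3.1 and 8.1.1, which the document leaves open.

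For the clinical summaries and the non-inferiority comparison, the fault is that a complier, complete-case set chosen after randomisation is the only stated basis. Bias is a risk, not a demonstrated effect. It is plausible because adverse events and voluntary withdrawal lead to removal. The shifts of 0 to 0.75 PHQ-9 points shown above come from assumed gaps and deletion fractions, and the documents fix neither size nor direction. If adherence and completion are both just at their criteria, the analysed number per arm would be about 21 to 26, against the 30 intended.

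**What to change.** Reword section 8.4 along these lines:

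1. Adherence, completion and safety use all randomised participants as the denominator, overall and by arm. A missed assessment or stopped treatment counts as not completing. State that the deletion rule does not apply to these outcomes.
2. Clinical outcomes and the non-inferiority comparison are summarised by assigned arm, using all observed data regardless of adherence. The amount of missing data, and the reasons for it, are reported by arm and time point. Descriptive summaries are enough for the scales, given the plan in 8.1.2; no repeated-measures model is required.
3. The complier-only analysis is kept as a labelled sensitivity analysis, or as the companion analysis for non-inferiority.

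The cost is a paragraph of wording. Reported feasibility rates may be less favourable. Data after withdrawal can be used only where they were collected, so the change does not by itself recover outcomes in people who leave the study.

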### Plans to give access to the full protocol, participant level-data and statistical code

8.5

Study datasets are available from the corresponding author upon reasonable request.

## Oversight and monitoring

9

### Adverse event reporting and harms

9.3

The study is not expected to result in serious adverse reactions and the risk assessment will be monitored by clinicians. In the event of an adverse reaction caused by aromatic sniffing, we will promptly treat or withdraw the participant from the study. In the meantime, we will record the details in the case report form.

### Plans for communicating important protocol amendments to relevant parties (e.g. trial participants, ethical committees)

9.5

All revisions will initially be discussed internally by the steering committee to reach a consensus before being submitted to the hospital’s ethics committee and the research department. Upon approval, a formal document detailing the modifications to the protocol will be shared with all relevant parties, with an electronic version available upon request. Any deviations from the protocol will be documented by the trial manager and signed off by the principal investigator. This document will then be stored alongside all other trial documentation. Following approval from the steering committee, research department, and ethics committee, the trial manager will make the necessary updates to the clinical trial application.

## Dissemination plans

10

A summary of the RCT outcomes will be compiled and emailed to participants who expressed interest in the results on their consent forms. The findings will be disseminated through articles in peer-reviewed journals and presentations at both national and international conferences. Additionally, results will be presented to other hospitals for sharing with their medical staff upon request. Data will be made available for reasonable requests.

## Discussion

11

The high prevalence of PSD not only severely affects the quality of life and overall recovery of the patient, creating a vicious cycle of recovery, but also creates both mental and material stress for the patient’s caregivers (50). Currently, the treatment of PSD is based on conventional treatments, especially medication and psychotherapy, with CBT often considered a “gold standard” treatment option due to its effectiveness. However, CBT requires the involvement of a professional psychotherapist, and it is difficult for patients to achieve self-management of their illness.

Aromatherapy can address some of the shortcomings of CBT, offering potential benefits in managing PSD. It can be self-administered, promoting patient autonomy and self-care. Previous studies have shown that aromatherapy can alleviate symptoms of depression, anxiety, and sleep disturbances, but there is limited research on its specific effects on PSD. Furthermore, previous studies often rely on subjective assessment scales, lacking objective indicators related to brain function. This study aims to fill that gap by using a multimodal assessment approach, including brain function measurements through EEG and fNIRS, to enrich the objectivity of PSD assessments.

This pilot study aims to provide preliminary data on the feasibility and the efficacy of mixed herb aromatherapy inhalation for treating PSD. The feasibility outcomes, including recruitment rates, adherence rates, and participant feedback, will help identify potential challenges and inform the design of future large-scale randomized controlled trials. The insights gained from brain function assessments using EEG and fNIRS will contribute to a deeper understanding of the mechanisms underlying the therapeutic effects of aromatherapy. This study has the potential to open up new treatment avenues for PSD, offer personalized treatment options, promote patient self-management, and address practical issues such as the acceptability of aromatherapy among patients.

This study will assess the feasibility of conducting aromatherapy interventions in a clinical setting, so as to provide valuable insights for designing larger-scale randomized controlled trials. The use of culturally relevant plant powders for aromatherapy could enhance participant motivation and compliance. In this context, “culturally relevant” refers to the selection of plant powders that align with traditional Chinese medicine practices and cultural preferences, which may increase the acceptance and adherence of Chinese participants. However, this approach may limit generalizability to other populations where different forms of aromatherapy are more commonly used.

Several limitations should be noted. One limitation is the difference in the amount of intervention time between the two groups. CBT is delivered twice a week at 30 minutes per session, while aromatherapy is implemented daily at 30 minutes per session. The primary obstacle lies in the nature of the interventions: CBT sessions are typically supplemented by homework assignments that patients complete independently between sessions, whereas aromatherapy involves daily inhalation sessions to maintain consistent therapeutic effects. Harmonizing these frequencies posed significant challenges. CBT requires professional involvement and structured sessions, which cannot be easily increased in frequency without additional resources and potential patient burden. In contrast, daily aromatherapy sessions are designed for regular self-administration. This discrepancy in intervention frequencies was unavoidable within the constraints of this study. Future studies could explore ways to equalize intervention times or investigate the dose-response relationship for each treatment modality.

Another limitation is the lack of data on physical function. The course and trajectory of PSD may be affected by the trajectory of physical recovery. Since this study does not collect data on physical function, it cannot control for these confounding factors. Collecting physical function data was not feasible due to resource constraints and the study’s primary focus on mental health outcomes. Addressing both the collection of physical function data and the harmonization of intervention frequencies was not possible due to limited time, funding, and personnel. These constraints made it challenging to extend the study scope beyond mental health outcomes. Future studies should include assessments of physical function to provide a more comprehensive understanding of the factors influencing PSD. This would provide a more holistic view of PSD treatment and help control for various confounding factors.

The follow-up period is also a potential limitation. This study includes a follow-up visit after 4 weeks, considering factors such as the duration of patient hospitalization. A longer follow-up period would allow for the assessment of long-term effects of the interventions and help determine the sustainability of the treatment benefits. Future research should consider extending the follow-up period to better understand the long-term impact of aromatherapy and CBT on PSD.

Participant selection bias may be present since the study is conducted in a single rehabilitation hospital in Shanghai, limiting the generalizability of the findings to other populations or regions. The placebo effect might also influence outcomes, particularly in the aromatherapy group. Individual differences in olfactory sensitivity and preference for certain scents may affect the efficacy of aromatherapy. Lastly, psychosocial factors such as social support, stress levels, and coping mechanisms, which can influence depression outcomes, are not extensively accounted for in this study.

Additionally, the issue of cultural relevance is a notable limitation. While the use of culturally relevant plant powders may enhance compliance among Chinese participants, it may limit the generalizability of the findings to other populations where different forms of aromatherapy are preferred.

An additional consideration for future research is the cost-effectiveness of aromatherapy compared to CBT. Health economics and cost-effectiveness analyses should be conducted to determine whether aromatherapy provides a more economical treatment option without compromising efficacy. Such analyses could include direct costs (e.g., treatment expenses) and indirect costs (e.g., time off work, caregiving costs), offering a comprehensive view of the economic impact of each therapy. This is particularly relevant in healthcare settings where resource allocation and cost management are critical.

Despite these limitations, this study provides valuable preliminary data and insights that could inform future research and contribute to the development of more effective treatments for PSD. Patients with PSD are encouraged to actively participate in self-management in their daily lives, learn to apply aromatherapy to manage depressive symptoms, and form a virtuous cycle of recovery. Additionally, through EEG and fNIRS, we aim to understand more deeply how aromatherapy affects brain activity, revealing its mechanism of action in depression treatment and stimulating further research on PSD treatment.

## Trial status

12

The research will start in April 2024 and is expected to end in April 2025. This study protocol is in its first version, registered in Chinese Clinical Trial Registry on 4 January 2024. (ChiCTR2400079491.)

## Ethics statement

This study received approval from the Ethics Committee of the Second Rehabilitation Hospital of Shanghai(approval number: 2023-20-01) and was registered with the China Clinical Trial Registration Center in January 2024 (registration number: ChiCTR2400079491). All participants are required to sign a written informed consent form in accordance with the Helsinki Declaration prior to their involvement.
